Project Title: Assessing Gait And Balance Using Body Worn Sensors: Does A Successful Clinical Intervention Also Improve Gait And Balance?

Background

Gait and balance disorders are frequently found in older adults and patient populations [1-4]. They are associated with increased morbidity and mortality, as well as reduced level of function and limited quality of life [1-4]. Changes in balance and gait are usually multifactorial in origin and require a comprehensive assessment to determine contributing factors and targeted interventions [5]. In older adults alterations in gait and balance should not be viewed as merely an inevitable consequence of aging but are frequently related to underlying medical conditions [3, 5]. Gait changes such as diminished stride length, increased double limb support and stepping variability are common in patients with a variety of diseases such as Parkinson's disease (PD), diabetic neuropathy, knee and hip osteoarthritis, or hemiplegia/hemiparesis [5, 6].  Pain caused by osteoarthritis or intermittent claudication may also lead to gait and balance alterations.

Early identification of gait and balance disorders and appropriate intervention may prevent dysfunction and loss of independence. Successful intervention requires a detailed analysis of clinically relevant biomechanical parameters related to motor control during ambulation. Thus far, quantification of such parameters has been performed by optical motion measurement systems, force plates, or specific walkways for gait analysis. These assessments, however, are often not feasible during clinical practice, as they are time consuming, cost intensive, and require extensive laboratory equipment. Also, by the short walking distance offered by laboratory based-technology, it is difficult to measure the variability of gait which is important for maintaining balance and responding to different walking challenges [7].

Human body motion is traditionally captured using standard optic, magnetic or sonic technologies [8]. However, in recent years, body-wearable sensor technology based on electro-mechanical sensors (MEMS) has provided a new avenue for accurately detecting and monitoring body motion and physical activity of an individual under free conditions [8-10]. Unlike laboratory-based instruments, which need a dedicated controlled space, the wearable sensors can be used just about anywhere [8]. These are highly portable and do not require stationary units such as a transmitter, receiver or cameras. In addition, these sensors are much cheaper than sonic, magnetic and optical motion capture devices [8]. They are easy to set up and use, and do not require highly skilled operators. In particular, combination of multiple accelerometers, angular rate sensors (gyroscopes), and magnetometer show a promising design for a hybrid kinematic sensor module for measuring the 3D kinematics of different body segments [11]. These sensors incorporated with a high speed data acquisition system enable measuring and recording of 3D body segment motion with sample frequency up to several hundred hertz with lower cost than camera based systems.

Our team has designed and validated several algorithms based on body worn sensors for various clinical applications. These areas include studying the spatio-temporal parameters of gait [8, 10, 12, 13], joint and segment angles (kinematics) [11, 14-16], monitoring spontaneous daily physical activity [17-24], and evaluating the fear of falling [25], and risk of falling [26]. One of the main advantages of body-worn sensors compared to laboratory-based measuring systems is that they are ambulatory and can be used in free conditions continuously over long periods of time [10].

Assessing gait and balance using wearable sensors

The aim of the present study is to implement two validated technologies based on wearable sensors named LEGSys [10, 12, 7] and BalanSens [11] for assessing respectively spatio-temporal parameters of gait and postural control in a clinical setting together with other clinically routine assessment (Figure 1). We may utilize some ancillary non-invasive tools such as a heat sensitive thermal camera, pressure sensitive foot insoles and a digital camera to aid in collecting additional data as described in later sections. Our specific aims are twofold, first we aim to explore whether and how a disorder, which may impact motor function such as diabetes, Parkinson, Stroke, etc. may impact gait and balance. Second, we will explore whether a routinely used clinical intervention can enhance gait and balance parameters.

The LEGSys device uses five sensor modules, respectively attached to right and left anterior shins, right and left anterior thighs, and posteriorly to the lower back. Each sensor measures the angular velocity of the segment around the medio-lateral axis (flexion-extension). The method for calculating spatio-temporal parameters of gait and balance has been described in detail in previous publications [8, 12, 27].

[figure not shown]

[figure not shown]

Figure 1. Wearable sensor technology used in the planned study to measure gait (left picture) and postural control (right picture).

BalanSens is based on widely-available kinematic sensors (i.e. accelerometer, gyroscope and magnetometer). The system measures ankle and hip motion in three dimensions (3D). We have also integrated the resulting data into a two-link biomechanical model of the human body for estimating the 2D sway of the center of mass (COM) in anterior-posterior (AP) and medial-lateral (ML) directions. To evaluate the best postural strategy for maintaining balance, a reciprocal compensatory index (RCI) was defined which quantifies how the movement around hip could compensate for the movement around ankle for reducing the variation of COM [11]. RCI values near zero represent a good postural control strategy (i.e. negative correlation between hip and ankle movements), RCI values more than one represent inappropriate postural control strategy (i.e. positive correlation between hip and ankle movements leading to increase the variation of COM and consequently fall accident), and RCI values near to one indicate there is no correlation between the movement of ankle and hip joints [11].

In addition to the body worn sensor systems, we will use insoles for measuring plantar pressure [Tekscan, Boston, MA] which might be related to specific diseases such as diabetes or neuropathy. Furthermore we will collect a set of relevant clinical variables including the Short Falls Efficacy Scale-International [28], Short Form Health Survey (SF-12) [29], the 5-chair rise test [30], the Cervical Spine Baseline and Cervical Spine Followup Survey, and the Lumbar Spine Baseline and Lumbar Spine Followup Questionnaires. These surveys will be conducted initially by written administration. However, we eventually will conduct them utilizing an electronic system such as Dynamic Clinical Systems interfaced with EPIC as part of standard care.

*Sample size estimation and power analysis:*

We also calculated the sample size based on our pilot study [31] using the same balance training paradigm. The results demonstrated that ankle reaching task is beneficial to improve balance by reducing the area of COM sway as well as improving the reciprocal coordination between ankle and hip movements. According to our results, we must recruit 15 patients to demonstrate a significant improvement after the proposed balance training program by assuming a power of 80% and alpha equaling 0.05. We will recruit 10 additional subjects (five per group) to compensate for potential drop out samples.

*Analysis plan:*

P-values of 0.05 or less will be considered statistically significant based on a two-sided test unless otherwise noted. All variables will be tabulated descriptively at each scheduled time point. For each continuous variable, the analyses will include the mean, standard deviation, minimum and maximum. For each categorical variable, the summary will include frequencies and percentages. Each variable will be analyzed using all available data. Baseline variables will be summarized using descriptive statistics.

To determine whether gait, balance, and physical activity variables change due to intervention (for instance, due to the balance training as described above), within-subject analyses of variance (ANOVA’s) will be employed. We assume that a successful intervention is also helpful to improve subjects gait, balance, and physical activity. Then sensor-derived movement variables should change substantially from baseline to the end of the intervention. For example, the range of motion of COM and RCI values should be reduced and gait velocity should be increased. Next, for all continuous variables, pretreatment scores will be regressed on post-treatment scores to form residualized change scores (e.g. VPT, monofilament test, pain intensity, A1C, etc). Correlations will then be generated among these scores to determine whether changes in sensor-derived movement factors are related appropriately with increases in (clinically assessed) functional capacities and self-report measures of activities, mood, socializing, etc. ANOVA test will be used to examine significant difference between intervention and sham group (if there is a sham group) or between patients and control group for age and BMI. Additional analyses will examine the degree to which early-treatment changes in cognitive variables and functional capacity variables (representing functional restoration processes) predict late-treatment changes in moving ability post intervention. Such analyses will also allow to elucidate the relative contributions fear of falling (assessed using FES score); and/or and range of motion (assessed using body worn sensors) made to bringing about clinically meaningful changes in gait balance control. Moderator effects will also be examined for exploratory purposes. Using gender as an example, mixed design ANOVA’s will be conducted to determine whether gait and balance factors change over the course of treatment at different rates or with different patterns for men and women. Additional analyses will test whether changes in gait and balance variables predict changes in clinically important outcome factors (e.g., fear of falling (FES), quality of life (SF12), adverse events, etc) depending on gender.

*References:*

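### The planned within-subject ANOVA does not, in its classical form, deliver the protocol's all-available-data rule: subjects without a post-intervention value add nothing to the change estimate

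*Protocol*

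**What the plan says.** Under Analysis plan, the protocol sets a data rule: "Each variable will be analyzed using all available data". The sentence stands among sentences on descriptive tabulation, but it speaks of analysis and is not limited to tables.

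The same section then names the test of the intervention effect: to see whether gait, balance and activity variables "change due to intervention (for instance, due to the balance training as described above), within-subject analyses of variance" will be used. Mixed-design ANOVA is named for moderators such as gender. Residualized change scores are also planned, and these need both a pre and a post value. Nothing says how a subject with no post-intervention value enters any of these analyses.

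Under Sample size estimation and power analysis, loss of subjects is foreseen: "we must recruit 15 patients to demonstrate a significant improvement after the proposed balance training program", and "We will recruit 10 additional subjects (five per group) to compensate for potential drop out samples". No dropout rate is given.

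**The concern.** A classical within-subject ANOVA is built on each subject's own differences between the modelled visits. A subject who leaves after baseline has no difference to offer, so either that subject is dropped or the method must change. The protocol promises one thing and names a procedure that ordinarily does another, with no rule for settling it, so the choice could be made after the data are seen.

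This touches the analysis that serves the second aim, whether a clinical intervention improves gait and balance. In a balance-training study it is plausible, though the protocol does not say so, that those who leave differ from those who stay. If leaving is related to the change, the completers' mean change is not the mean change of the subjects enrolled.

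**Working it through.** **1. The plan's own figure.** The 15 cannot be reproduced forward, because the protocol gives no effect size or SD, only a reference to the pilot study. Solved backwards at 80% power and alpha 0.05, a two-sided paired t-test with n = 15 implies a mean change of 0.78 SD of change. Two-sidedness is stated for the analysis ("P-values of 0.05 or less will be considered statistically significant based on a two-sided test unless otherwise noted"), not explicitly for the sample size. If 15 is per group in a two-sample comparison, the implied difference is 1.06 SD. The 0.78 is used below only as a yardstick.

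**2. The loss the margin would allow.** Share = extra / (required + extra).
- If 15 is the total: 10 / (15 + 10) = 10/25 = 40%. The ANOVA would rest on 15 of 25.
- If 15 is per group: 5 / (15 + 5) = 5/20 = 25%. The ANOVA would rest on 30 of 40.

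**3. Completers-only bias when dropout depends on baseline.** Assumptions, none of them from the protocol: baseline and post values are normal with equal variance and correlation r = 0.5 to 0.8; a dropout score has correlation k = 0.7 with worse baseline; the share p with the highest scores leaves. With c the (1 − p) normal quantile and φ the normal density:
- shift of the completers' mean baseline = k × φ(c) / (1 − p), in baseline SDs, towards better balance
- expected change bias = (1 − r) × shift, towards worsening, because completers regress back towards the mean
- SD of change = √(2(1 − r)), so bias in SD of change = shift × √((1 − r)/2)

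| Loss p | φ(c) | φ(c)/(1 − p) | × 0.7 | Bias, r = 0.5 (× 0.500) | Bias, r = 0.8 (× 0.316) |
|---|---|---|---|---|---|
| 25% | 0.318 | 0.424 | 0.297 | 0.148 | 0.094 |
| 40% | 0.386 | 0.644 | 0.451 | 0.225 | 0.143 |

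A constant true change only shifts the post values and leaves the bias as it is. Against the 0.78 yardstick, the smallest and largest values are 0.094/0.78 = 12% and 0.225/0.78 = 29%. A separate illustration with logistic dropout (slope 1 per baseline SD, r = 0.5 to 0.7, true change 0.78 SD) agrees in direction and size: completers recover 0.79 to 0.89 of the true change.

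**4. Other dropout mechanisms.** Large-sample simulation, same r, p and k, bias in SD of change:

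| Dropout depends on | Completers only | Likelihood, all observed data |
|---|---|---|
| Baseline | 0.09 to 0.23, understates improvement | within 0.002 |
| Mean of pre and post | 0.00 | 0.11 to 0.25, overstates |
| Post value | 0.09 to 0.23, overstates | 0.20 to 0.36, overstates |

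If dropout is completely at random, both are unbiased. What matters for completers is whether dropout is related to the change. If post equals baseline plus independent noise, even baseline-driven dropout causes no bias.

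**The case against.** **The sentence may mean less.** It can be read as available-case analysis variable by variable: a subject missing one measure stays in the analysis of the others. A completers ANOVA for each variable fits that reading. This stands, and it is why the point is a tension and not a contradiction.

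**Missing-data detail belongs in the SAP, which is not shown.** This stands for imputation and covariance structure. It does not answer the point, because the protocol itself fixes both the data rule and the method. The protocol also never says that incomplete subjects are dropped; that follows from the classical method, and a likelihood-based repeated-measures fit would keep them.

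**The bias is modest and its sign is not fixed.** With 15 completers the standard error of the mean change is 1/√15 = 0.26 SD, larger than every completers bias above. In the baseline-driven case the error goes against finding an improvement. Both statements are right.

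**Stronger readings that the protocol does not support.** A reader might infer that:
- 25% to 40% dropout is expected. It is only a margin worked out from an ambiguous sentence, and is consistent with simply aiming for 15 evaluable subjects.
- anyone missing any visit is lost. For the contrast of baseline with end of intervention, a missed interim visit excludes nobody.
- completers are unbiased only if dropout is unrelated to baseline, or that a mixed model always repairs the bias. The second table shows otherwise on both counts.

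**Conclusion.** The point holds in limited form. The named ANOVAs, in classical form, do not deliver the rule of using all available data, in a trial that plans for losses. The possible cost is a completers-only change off by about 0.09 to 0.15 SD of change at 25% loss and 0.14 to 0.23 SD at 40%, against improvement, if subjects with worse baseline balance leave. These sizes rest on assumed correlations and an assumed dropout mechanism; the protocol gives none of them. If dropout is unrelated to the change, completers are unbiased. It is a worthwhile correction to the plan, not a flaw that invalidates the trial, whose aims are framed as exploratory.

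**What to change.** In the Analysis plan, replace the within-subject and mixed-design ANOVA with a linear mixed model for repeated measures, fitted by REML to all observed visits, with Kenward-Roger degrees of freedom for the small sample. Include group and group-by-time terms only if there is a comparison group, since the protocol makes a sham group conditional; gender and gender-by-time terms serve the moderator analysis. Report the completers-only ANOVA as a sensitivity analysis. Say that the model relies on data missing at random and can lie further from the truth than completers if dropout depends on the unobserved post value; that is the reason for showing both.

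In the sample size section, state whether 15 is the total or per group, and what dropout rate the extra 10 subjects assume.

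The cost is a few sentences and a different standard procedure; no further data are needed. If the sponsor keeps the ANOVA as the main analysis, the least change is to limit the all-available-data rule to the descriptive tables and to call the ANOVA a completers analysis.

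### The residualised change regression is stated in the wrong direction, so the scores formed are not baseline-adjusted change and their correlations can mislead either way

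*Protocol*

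**What the plan says.** The Analysis plan in the protocol first uses within-subject ANOVAs to test whether gait, balance and activity measures change with the intervention. It then turns to change scores, for all continuous variables: "pretreatment scores will be regressed on post-treatment scores to form residualized change scores". The examples listed are vibration threshold, monofilament test, pain intensity and A1C. The next step is: "Correlations will then be generated among these scores to determine whether changes in sensor-derived movement factors are related appropriately" to increases in functional capacity and to self-report measures.

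In ordinary usage, regressing Y on X makes Y the dependent variable and X the predictor. Here the pretreatment score is therefore the dependent variable. Nothing else in the protocol states the opposite direction. The protocol is the only document available for this review.

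**The concern.** A residualised change score is what remains of the post-treatment value once the part predicted by baseline has been removed. Its purpose is to be free of baseline. The regression as written removes from the baseline value the part predicted by the outcome. What is left is free of the post-treatment value and still carries baseline.

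The correlations among these scores are meant to show whether patients whose sensor measures improve are also those who improve clinically. If the scores carry baseline, two measures that merely go together before treatment can appear to change together. Conversely, a real link between changes can be diluted. Because the rule covers every continuous variable, it reaches every correlation built this way.

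**Working it through.** **The plan's own figure.** The protocol gives no figure for these scores or correlations. Its only related number is the 15 patients under Sample size estimation and power analysis. No effect size or standard deviation accompanies it, so it cannot be reproduced. It can only be back-solved: a paired two-sided t-test with 80% power at 15 patients implies a standardised effect of 0.78. The present point does not depend on it.

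**Inputs from the protocol.**
- Direction of regression: pre on post (Analysis plan).
- Test level: "P-values of 0.05 or less will be considered statistically significant based on a two-sided test unless otherwise noted".
- Number of patients: 15, and "We will recruit 10 additional subjects (five per group) to compensate for potential drop out samples". This is read here as 15 + 10 = 25 in total; n = 15 is shown as a lower case.

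**Inputs assumed, because the protocol gives none.**
- r, the pre-post correlation of a measure, taken from 0.3 to 0.9 and common to both measures.
- ρ_b, the correlation of the two measures at baseline.
- ρ_c, the correlation of their correctly residualised changes.
- No cross-lagged effects: the baseline of one measure does not predict the residualised change of the other.

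**Step 1: what the score contains.** On standardised scores, write post = r·pre + √(1−r²)·e, where e is the correct residualised change. The residual as written is

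pre − r·post = (1−r²)·pre − r√(1−r²)·e.

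Dividing by its standard deviation √(1−r²) gives √(1−r²)·pre − r·e. Its correlations are therefore:
- with post: 0
- with baseline: √(1−r²)
- with the correct score: −r
- with raw change (equal variances): −√((1+r)/2)

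| r | with baseline | with correct score | with raw change |
|---|---|---|---|
| 0.3 | 0.95 | −0.3 | −0.81 |
| 0.5 | 0.87 | −0.5 | −0.87 |
| 0.7 | 0.71 | −0.7 | −0.92 |
| 0.9 | 0.44 | −0.9 | −0.97 |

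**Step 2: correlation between two such scores.** From the last expression,

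correlation as written = (1−r²)·ρ_b + r²·ρ_c,

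so the bias is (1−r²)·(ρ_b − ρ_c). The weight on the baseline correlation, 1−r², is 0.91, 0.75, 0.51 and 0.19 for r = 0.3, 0.5, 0.7 and 0.9.

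**Step 3: size.** Example at r = 0.7:
- ρ_b = 0.5 and ρ_c = 0 gives 0.51 × 0.5 = 0.255 where the true value is 0.
- ρ_b = 0 and ρ_c = 0.5 gives 0.49 × 0.5 = 0.245 where the true value is 0.5.

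Rejection rates come from 20,000 simulated normal data sets per setting, two-sided 0.05.

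| Setting | r = 0.3 | 0.5 | 0.7 | 0.9 | Correct direction |
|---|---|---|---|---|---|
| ρ_b = 0.5, ρ_c = 0: expected correlation | 0.455 | 0.375 | 0.255 | 0.095 | 0 |
| false positives, n = 25 | 61% | 43% | 21% | 6.5% | about 5% |
| false positives, n = 15 | 35% | 24% | 12% | 5.5% | about 5% |
| ρ_b = 0, ρ_c = 0.5: expected correlation | 0.045 | 0.125 | 0.245 | 0.405 | 0.5 |
| power, n = 25 | 5% | 8% | 19% | 49% | about 70% |
| ρ_b = 0.3, ρ_c = 0.5: expected correlation | 0.318 | 0.350 | 0.398 | 0.462 | 0.5 |
| power, n = 25 | 33% | 39% | 49% | 63% | about 70% |
| ρ_b = ρ_c = 0.5: expected correlation | 0.5 | 0.5 | 0.5 | 0.5 | 0.5 |

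In the last row the power at n = 25 is about 71% in both directions.

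**The case against.** The strongest defence is that this is a slip of wording. The protocol names the intended product and its purpose, and an analyst who knows the method would compute it correctly. That is plausible, and the error rates above apply only if the sentence is followed literally. But nothing in the protocol corrects it, and an analyst who does follow it gets the wrong residual.

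A second defence is that the score as written still tracks raw change closely, with the sign reversed. It does, but the correct score tracks raw change equally well (+√((1+r)/2)), so nothing is gained. Simple post-minus-pre correlates with baseline at −√((1−r)/2), which is 0.39 in size at r = 0.7 and 0.22 at r = 0.9. The score as written has 0.71 and 0.44. It is more tied to baseline than no adjustment at all.

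Three stronger readings are tempting and not supported.
- *The scores mainly carry baseline.* Baseline makes up more than half the variance only when 1−r² > 0.5, that is r below about 0.71. At r = 0.9 its share is 19%. From r = 0.5 upward the score follows raw change at least as closely as it follows baseline.
- *The correlations are certainly biased.* The bias depends on ρ_b − ρ_c, is zero when the two are equal, and can go either way. The protocol gives neither value.
- *The planned correlations come out with the wrong sign.* They are taken among scores that are all reversed, so the two sign changes cancel. A wrong sign could arise only if a reversed score were set against something not built this way, a use this sentence does not specify.

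**Conclusion.** The direction is wrong as written, and that conclusion needs no assumption. Each score is uncorrelated with the post-treatment value and correlated √(1−r²) with baseline, so it is not baseline-adjusted change. The size of the consequence does rest on assumptions: a common r, no cross-lagged effects, and chosen values of r, ρ_b and ρ_c. Within these it ranges from none (ρ_b = ρ_c), through near-harmless (6.5% false positives at r = 0.9), to severe (61% at r = 0.3, or power down from about 70% to 5%).

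A reader might infer that the trial's main conclusions are at risk. The protocol does not support that. Change after the intervention is tested by within-subject ANOVAs, and the sample size statement, "we must recruit 15 patients to demonstrate a significant improvement after the proposed balance training program by assuming a power of 80% and alpha" of 0.05, concerns that improvement. Neither uses these scores. The protocol also plans analyses of whether gait and balance changes predict outcome changes, and does not say that they rest on these residuals. The point is one that should be fixed, confined to the change-to-change correlations.

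**What to change.** Exchange the two terms in the sentence. For each continuous variable, the post-treatment score should be the dependent variable and the pretreatment score the predictor, with the residual (observed minus predicted post-treatment score) used as the residualised change score. Any SAP should carry the same direction. The cost is one sentence of wording; no data collection, recruitment or sample size is affected.

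### The change-score correlations carry no term for group; if more than one arm or disease cohort enters them, they can be non-zero with no link within any group

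*Protocol*

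**What the plan says.** The Analysis plan first uses within-subject ANOVAs to test whether the sensor measures change with the intervention. It then moves to association. For all continuous variables, "pretreatment scores will be regressed on post-treatment scores to form residualized change scores". The next step is: "Correlations will then be generated among these scores to determine whether changes in sensor-derived movement factors are related appropriately", that is, related to gains in clinically assessed function and in self-reported measures. Neither step names study arm, disease cohort or any other covariate, and no within-group version is described. A general sentence in the same section reads "Each variable will be analyzed using all available data".

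Groups appear elsewhere in the protocol:

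- *Sample size estimation and power analysis*: "We will recruit 10 additional subjects (five per group) to compensate for potential drop out samples", which implies two groups.
- *Analysis plan*: an ANOVA comparing "intervention and sham group (if there is a sham group) or between patients and control group for age and BMI". The sham group is conditional, and the comparison covers age and BMI only.
- *Aims*: the first aim is to explore whether and how "a disorder, which may impact motor function such as diabetes, Parkinson, Stroke, etc. may impact gait and balance".

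Gender is the only moderator named.

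**The concern.** Residualizing a measure on its own pre- and post-treatment scores does not remove a difference between arms in mean change. If the intervention moves both a sensor measure and a clinical measure in one arm and not in the other, treated participants tend to have high scores on both and untreated participants low scores on both. The pooled correlation is then positive even if, within each arm, a participant's sensor change says nothing about that participant's clinical change. Disease cohorts with different average change act in the same way.

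The protocol expects sensor measures to change substantially after a successful intervention, so the condition is not remote. At stake is the statement that sensor change tracks clinical change from participant to participant, which is what a reader would take from a significant correlation here.

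**Working it through.** **Inputs from the protocol.** Two-sided test at 0.05; 15 patients for 80% power; 10 more, five per group. The total is 15 + 10 = 25 if 15 is the whole sample, or 2 × (15 + 5) = 40 if 15 is per group.

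**The plan's own figure.** No figure is given for the correlations. The 15 patients cannot be reproduced, because no effect size, SD or test is stated. Solving backwards, 15 corresponds to a standardized effect of 0.78 for a paired t-test, or 1.06 for a two-sample t-test with 15 per arm. The first is a within-subject effect and cannot serve as an arm difference. The second is used below only as one illustrative value.

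**Assumptions, not in the documents.** Equal arms; zero correlation between the two changes within each arm; the same arm difference d on both measures, in within-arm SDs of the residualized change; and, for the simulation, a pre-post correlation of 0.6.

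**Formula.** With a share p in one arm, within-arm correlation r_w and arm differences d1 and d2:

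r = (r_w + p(1−p)·d1·d2) / √[(1 + p(1−p)·d1²)(1 + p(1−p)·d2²)]

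With p = 0.5, r_w = 0 and d1 = d2 = d, this becomes r = 0.25d² / (1 + 0.25d²):

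- d = 0.5: 0.0625 / 1.0625 = 0.06
- d = 0.8: 0.16 / 1.16 = 0.14
- d = 1.06: 0.2809 / 1.2809 = 0.22
- d = 1.5: 0.5625 / 1.5625 = 0.36

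If either d1 or d2 is zero, the numerator is zero and so is r.

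**Simulation.** Each score is residualized within the simulated sample and r is tested at 0.05 (20,000 or more runs per setting). Arms are 13/12 for N = 25 and 20/20 for N = 40.

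| d | mean r, post on pre, N = 25 | false positives, N = 25 | false positives, N = 40 |
|---|---|---|---|
| 0.5 | 0.06 | 6% | 6.5% |
| 0.8 | 0.13 | 10% | 13% |
| 1.06 | 0.21 | 17% | 27% |
| 1.5 | 0.36 | 42% | 65% |

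The simulated r can fall slightly below the closed form in samples of this size. The row d = 1.06 matches the reading of 15 per arm, so its natural partner is N = 40; the N = 25 entry is given for comparison.

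**Three checks on the scope.**

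- Arm included in both the residualization and the correlation: mean r about 0.00, false positives 4.6 to 5.2% in every two-arm setting tried.
- One treated group of 25: false positives about 5% whatever the mean improvement.
- Regression as literally worded, with pre as the dependent variable, N = 25: r of 0.04 and 5.6% false positives at d = 0.8; r of about 0.10 and 7.0% at d = 1.5.

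**The case against.** The strongest reply is that pooling is never stated. The sentence on available data is general and does not define who enters the correlations, and an analysis plan that is not shown could restrict or stratify them. The sham group is conditional. The protocol describes no treatment for the control group, so that group may supply no change scores. The list of disorders belongs to the first aim, whereas change after intervention is the second; the pilot behind the sample size concerned diabetic peripheral neuropathy alone. All of this stands, and it makes the point conditional. It does not remove the point: the protocol names the method, simple correlation of residualized scores, and foresees two groups without saying how they enter.

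A reader might infer that the correlations are definitely planned over all participants and will therefore show false links. The text does not support that, and with one treated group nothing is inflated. A reader might also infer that these correlations decide the title question. They do not: whether gait and balance improve is addressed first by the within-subject ANOVAs, and the correlations follow.

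It is also fair to say that a pooled correlation legitimately describes measures moving together, including movement produced by treatment. That supports reporting it, but not reading it as evidence of a link between the changes of individual participants.

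Finally, the size depends on how the score is formed. Under the literal pre-on-post wording the inflation is slight. Correcting that direction without adding arm would bring in the larger figures.

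**Conclusion.** The point holds conditionally. The specified correlations have no group term, and they can be non-zero with no within-group link if more than one arm or cohort enters and the groups differ in mean change on both measures. The inflation is negligible to small for d up to 0.5 and becomes material from about d = 0.8 to 1.0 with conventionally formed scores. It is absent with a single group, or when either measure shows no group difference. Every value of d, the equality of d across the two measures and the pre-post correlation of 0.6 are assumptions; the protocol gives the expected direction of change and no magnitude. Mixing disease cohorts in the change-score analysis is neither stated nor excluded. This should be settled before analysis, together with the direction of the residualizing regression.

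**What to change.** In the Analysis plan:

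1. State which participants enter the change-score correlations.
2. Where more than one arm or disease cohort enters, include arm and cohort in both the residualization and the correlation, which gives a partial correlation.
3. Report the within-arm and pooled estimates beside it, and base the statement that sensor change tracks clinical change on the adjusted estimate.
4. If a regression is used instead, include the baselines of both the sensor and the clinical measure. A model that omits the clinical baseline is not equivalent to the partial correlation.
5. In the same edit, reverse the residualizing regression so that post-treatment scores are regressed on pre-treatment scores.

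The cost is a change of wording and one or a few degrees of freedom. No extra data are needed.
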